#### Post‐Implementation Monitoring

3.7.3

Ongoing assessment of protocol adherence, measured as the testing‐intensity outcomes defined under Secondary Estimands and analyzed as specified in the Statistical Analysis Plan.Safety monitoring and adverse event tracking.Periodic reinforcement and education sessions.Every month, data on overall mortality will be collected from the SIR and used to monitor deaths until the last patient has completed final follow‐up.

## Outcomes

4

### Primary Estimand

4.1

*Following the ICH E9(R1) estimand framework*:

The ICH E9(R1) addendum is the International Council for Harmonisation guideline on statistical principles for clinical trials, whose addendum (R1) defines the estimand framework used to provide a precise description of the treatment effect being estimated, including the handling of intercurrent events [33]. The primary estimand is defined as follows:

The population comprises adults (≥ 18 years) admitted to a participating ICU during the study period. The treatment conditions are management during an intervention period (the CW bundle) versus management during a control period (standard practice at each ICU). For patients with more than one ICU admission during the study period, each care episode is analyzed under the exposure condition prevailing at the time of that admission, and the resulting within‐patient correlation is accounted for in the analysis model.

The endpoint is all‐cause mortality within 30 days of ICU admission, ascertained through SIR's linkage to the Swedish population register. The population‐level summary measure is the adjusted absolute risk difference in 30‐day mortality (intervention minus control). Intercurrent events are expected to be rare: outcome ascertainment through the population register is essentially complete, and reversion of a cluster from intervention to standard care is not planned; intercurrent events are handled under a treatment‐policy strategy, consistent with the intention‐to‐treat principle.

### Secondary Estimands

4.2

Secondary outcomes are defined per ICU care episode. ICU length of stay is the time from ICU admission to ICU discharge or death. The durations of invasive mechanical ventilation, noninvasive ventilation, and CRRT are the cumulative hours of each therapy during the ICU episode, as registered in SIR; because death precludes further accrual of these durations, they are analyzed in a time‐to‐event framework with death handled as a competing event. Unplanned ICU readmission is defined, per the SIR definition, as an unplanned return to intensive care within 72 h of ICU discharge, recorded as a binary outcome per discharged episode.

Testing‐intensity outcomes, referred to elsewhere in this protocol as process outcomes, are the number of ABG samples, venous laboratory tests, and chest radiographs per patient‐day.

The environmental outcome—climate impact expressed as carbon dioxide equivalents (CO_2_e, 100‐year global warming potential) attributable to blood gas sampling, laboratory testing, and chest radiography—will be estimated from the process‐outcome counts combined with published and supplier‐derived emission factors per test, with the functional unit being CO_2_e per patient‐day; a separate prespecified analysis plan will detail data sources, system boundaries, and methods, and this outcome is exploratory. Because death precludes the further accrual of tests and of their associated emissions, an intervention that increased early mortality would mechanically appear favorable on both testing intensity and CO_2_e. These outcomes are therefore subordinate to the primary safety outcome: they are interpreted as evidence of benefit only if non‐inferiority for 30‐day mortality is demonstrated, and if it is not, they are reported descriptively with no efficiency or environmental claim made. All such outcomes are expressed per patient‐day as well as per care episode, so that any shortening of the denominator through earlier death remains visible.

### Outcome Measurement

4.3

*Registry data collection*: Primary and secondary outcomes will be collected through SIR, which captures standardized data elements for all Swedish ICU admissions, including:
Demographics and comorbiditiesSeverity of illness, Simplified Acute Physiology Score (SAPS 3)Interventions and proceduresOutcomes and discharge statusUnplanned readmission within 72 h

*Local monitoring*: Participating sites will collect process outcomes through designated clinical monitors during specified monitoring periods:
Baseline period pre‐implementation (5 days)1‐Month post‐implementation (5 days)3‐Month post‐implementation (5 days)

#### Validation of Local Monitoring

4.3.1

High‐resolution electronic health data will be requested from clusters where available to allow more granular assessment of protocol adherence over the entire study period.An additional measure to validate the sampling performed by local clinical monitors is the documentation of departmental orders for vacutainer tubes and blood gas syringes.

Because a non‐inferiority design is vulnerable to a null result arising from non‐delivery rather than from true equivalence, intervention fidelity is treated as a precondition for interpreting the primary result. The fidelity criterion is an interpretive safeguard and not a definition of the analysis population: it does not determine which patients, clinicians, or clusters are analyzed, and the primary analysis remains an unconditional intention‐to‐treat comparison in which every care episode is analyzed according to the randomized state of its cluster at the time of admission, irrespective of local adherence. We prespecify that non‐inferiority will be interpreted as demonstrated only if the pooled reduction in testing intensity (ABG samples, venous laboratory tests, and chest radiographs per patient‐day) during intervention periods reaches at least 5% relative to the same clusters' control periods. The rationale is that a non‐inferiority finding on patient outcomes is informative only if the trial achieved a material separation between conditions: were testing to fall by, say, 1%, non‐inferior mortality would be near‐guaranteed irrespective of whether reduced testing is in fact safe. If the observed reduction falls below this threshold, the primary result will be reported as inconclusive with respect to the safety of CW implementation rather than as evidence of non‐inferiority. Because the criterion removes no care episode from the analysis population, it does not alter the power calculation.

### Sample Size and Power Calculations

4.4

It is unlikely that the implementation of the CW protocol will lead to improved ICU outcomes [22, 24], so we wanted to avoid superiority metrics. Therefore, we opted for a non‐inferiority design. Pragmatic elements of the present study that we need to address:
In Sweden, the CW concept is gaining traction, especially in the ICU setting. Thus, it is imperative that the present study is done rapidly. Some ICUs have already begun implementation of the CW concept and cannot be included.The present study would improve its power if it were performed over a 2‐year period, but this is not practically feasible, since both clinicians and policymakers advocate for a rapid implementation of CW.In order to more robustly assess the safety of CW, we will report multiple secondary outcomes in addition to the primary outcome: 30‐day mortality. ICU length of stay, time on invasive and noninvasive ventilation, time on CRRT, and unplanned readmissions add a high‐resolution layer of patient safety metrics.

With 38 ICUs included, covering 53% of all adult Swedish ICU admissions over the year (although this study runs for 13 months), the study findings will be broadly generalizable (37 ICUs following one withdrawal, as described under Section 2.5).

#### Non‐Inferiority Power Analysis

4.4.1

We conducted a non‐inferiority‐based power calculation for our primary outcome of mortality, using a non‐inferiority margin of 3%. The analysis is based on data from the SIR.

The choice of a 3‐percentage‐point margin was made on the following grounds. First, the intervention removes routine, non‐indicated testing while explicitly preserving all clinically indicated diagnostics, and the aggregate randomized and observational evidence on diagnostic‐test reduction in intensive care shows no signal of increased mortality [22]; a true effect approaching the margin is therefore considered implausible a priori. Second, mortality is deliberately complemented by more sensitive safety outcomes that would be expected to deteriorate before any mortality effect became detectable, together with monthly safety monitoring throughout the trial. Third, the margin must be weighed against feasibility: demonstrating non‐inferiority within a substantially narrower margin (e.g., 1–2 percentage points) would require a trial several times larger, running over multiple years, which is not achievable while ICUs are already adopting CW practice outside trial conditions; the present design represents the strongest randomized evidence obtainable before uncontrolled implementation makes a controlled evaluation impossible. On balance, the steering committee judged that, for an intervention with documented benefits in reduced iatrogenic anemia, reduced resource use and reduced environmental impact, a 3‐percentage‐point margin represents the largest mortality difference that could be considered clinically acceptable, while the a priori expected difference is null. The margin may also be set against those adopted in recent critical care non‐inferiority trials with all‐cause mortality as the primary outcome. EVERDAC, comparing early with deferred arterial catheterization in shock, used a margin of 5 percentage points against a control‐group 28‐day mortality of 36.9% [34]. BALANCE, comparing 7 with 14 days of antibiotic therapy for bloodstream infection, used 4 percentage points against a control‐group 90‐day mortality of 16.1% [35]; three earlier trials in that field used 10 percentage points. In absolute terms, the present margin is smaller than both. In relative terms, 3 percentage points against a baseline 30‐day mortality of 18% corresponds to a risk ratio of 1.17, which lies between the corresponding figures for EVERDAC and BALANCE. The choice of margin does not by itself determine what would justify a change in practice; that question is addressed in the Discussion. Expressed in absolute terms, a true effect lying exactly at the margin would correspond to approximately 670 additional deaths across the projected 22,428 care episodes. The trial is therefore designed to exclude, rather than to detect, harm of this magnitude, and the secondary safety outcomes together with monthly monitoring are intended to identify smaller signals earlier.

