
#### Power Calculation

4.4.2

Sample size was calculated using the swCRTdesign package in RStudio.

Parameters:

*Stepped wedge design*: As shown in Figure 1.
*Primary endpoint*: 30‐day mortality.
*Design*: Non‐inferiority trial.
*Number of patients per cluster and time period*: A total of 38 ICUs were included in the analysis. Two ICUs were merged into a single cluster because they share staff, resulting in *37 distinct clusters*. The stepped‐wedge design comprised *13 time periods*. Based on historical data, the total number of ICU admissions during the 13‐month study period was estimated to be *22,625 episodes*, derived from Swedish Intensive Care Registry admission data for the participating clusters over the corresponding calendar period [29]. Under these assumptions, the average number of ICU admissions per cluster and time period was calculated as 22,625 ÷ 13 ÷ 37 ≈ *47 admissions*.These are the parameters prespecified before recruitment opened. Following the withdrawal of one cluster, the corresponding figures are 22,428 episodes across 36 clusters and 13 periods, approximately 47 admissions per cluster‐period, a reduction of 0.9% that does not materially affect the power calculation, which has therefore not been repeated.
*Alpha level*: 0.025 (one‐sided 97.5% CI).
*Intraclass correlation coefficient (ICC)*: 0.009
○The ICC was calculated using historic data via a generalized linear mixed model. To account for differences in baseline mortality across ICU types, the model included:
A variable distinguishing ICU category [1, 2, 3].A variable indicating whether the ICU was a thoracic unit, which has distinct expected mortality rates.

*Treatment effect was assumed to be homogeneous across clusters*.
*No fixed time trends were assumed*.

*Non‐inferiority margin assumption for 30‐day mortality*: Based on historical data, the mean baseline 30‐day mortality across the relevant clusters was estimated at 18%, based on Swedish Intensive Care Registry historical data for the participating clusters [29]. The non‐inferiority margin was defined as an absolute risk difference of 3 percentage points. Assuming the same baseline mortality, this corresponds to a relative risk of 1.17 and an odds ratio of approximately 1.21.

*Power to demonstrate non‐inferiority under the assumptions stated above*: 89%. A Power > 80% will be considered acceptable to demonstrate non‐inferiority.

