Because the estimand is an absolute risk difference, adjusted marginal risks under intervention and control are obtained from the fitted model by regression standardization (g‐computation): the model is used to predict each episode's outcome probability under both treatment conditions, and these predictions are averaged over the trial population. The adjusted risk difference is the difference between the two standardized risks, with a 95% CI obtained by cluster bootstrap or delta method. Non‐inferiority is declared if the upper bound of the two‐sided 95% CI (equivalently the one‐sided 97.5% bound) for the adjusted risk difference (intervention minus control) lies below 3 percentage points. Intention‐to‐treat analysis behaves differently in a non‐inferiority trial than in a superiority trial. Whereas incomplete adherence biases a superiority comparison toward the null and is therefore conservative, in a non‐inferiority comparison it makes the two conditions more alike and so makes a conclusion of non‐inferiority easier to reach; intention‐to‐treat is in this sense anti‐conservative [37]. We therefore prespecify a per‐protocol analysis alongside the primary intention‐to‐treat analysis. The per‐protocol population comprises all control periods together with those intervention cluster‐periods in which the cluster's own testing intensity met the fidelity criterion; cluster‐periods during which the intervention was paused or modified under the provisions above are excluded from the intervention condition. The per‐protocol analysis uses the same model, covariates, and non‐inferiority margin as the primary analysis. A conclusion of non‐inferiority requires the upper confidence bound to lie below the margin in both analyses. Where the two are discordant, both are reported, and the discordance is discussed rather than resolved by rule. Realized testing intensity is reported for both conditions at cluster level so that the separation achieved is visible to the reader.

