## Discussion

7

The WICH‐ICU trial will address several important knowledge gaps in critical care and implementation science.

The WICH‐ICU trial will provide randomized evidence on the safety of systematically implementing CW recommendations in intensive care, an area where high‐quality evidence is currently scarce [22, 24]. By pairing 30‐day mortality with a set of more sensitive safety outcomes, and by embedding the intervention in routine care across a national registry, the trial is designed to detect any safety signal while remaining pragmatic and generalizable.

The design has several strengths. The stepped‐wedge approach maximizes statistical efficiency while ensuring that every site eventually receives the intervention; the registry‐based approach leverages a high‐quality, near‐complete national data infrastructure; cluster randomization minimizes contamination and reflects real‐world implementation; and the multi‐site design, covering roughly half of Swedish adult ICU admissions, enhances generalizability. The interventions are grounded in established professional recommendations, are designed for routine clinical use, and are supported by a local‐champion model that promotes sustainability.

The non‐inferiority margin defines the decision rule for a prespecified statistical hypothesis; it is not the threshold at which we would recommend a change in practice. Because the intervention removes routine testing rather than adding treatment, and because the benefits at stake are efficiency and environmental rather than clinical, the trade‐off is asymmetric: a mortality difference lying well within the margin could still be judged unacceptable for an intervention of this kind. We will therefore report the point estimate and the full confidence interval for the adjusted risk difference alongside the formal non‐inferiority conclusion, and we state in advance that a point estimate indicating excess mortality under the intervention would not, in our view, support de‐implementation of the targeted diagnostics even were the upper confidence bound to fall below 3 percentage points. As noted above, a true effect at the margin would correspond to approximately 670 additional deaths across the projected care episodes; a difference half that size would remain clinically material and will be reported as such.

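### The 3-point margin is called the largest clinically acceptable difference, but the Discussion disowns that meaning, and its point-estimate condition is missing from the decision rule, the benefit gate and the closing claim

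*Protocol article*

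**What the plan says.** All references are to the protocol article.

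- **4.4.1, Non-Inferiority Power Analysis.** The steering committee judged that the 3-point margin "represents the largest mortality difference that could be considered clinically acceptable". Reduced iatrogenic anemia is listed among the documented benefits it was weighed against. The section equates an effect at the margin with "approximately 670 additional deaths across the projected 22,428 care episodes". It also says the margin alone does not settle what would justify a change in practice, and refers that question to the Discussion.
- **5.2, Primary Analysis.** Non-inferiority is declared if the upper 95% bound "for the adjusted risk difference (intervention minus control) lies below 3 percentage points". The conclusion requires this in both the intention-to-treat and the per-protocol analysis. Section 4.3.1 adds a condition of at least a 5% reduction in testing.
- **7, Discussion, paragraph on the margin.** The margin is described as a statistical decision rule and not a practice threshold. The text then says that "a mortality difference lying well within the margin could still be judged unacceptable for an intervention of this kind", that "the benefits at stake are efficiency and environmental rather than clinical", and, after recalling the figure of about 670 deaths, that "a difference half that size would remain clinically material and will be reported as such". The estimate and full confidence interval will be reported. An excess point estimate would not, in the authors' view, support de-implementation even with the bound below 3 points.
- **4.2, Secondary Estimands.** Testing-intensity and CO2e results count as evidence of benefit only if mortality non-inferiority is shown. No other condition is named.
- **7, closing paragraph.** If non-inferiority is demonstrated, the results will support de-implementation. The point-estimate condition is not repeated.

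**The concern.** A value cannot be the largest acceptable difference if values well below it may be unacceptable. The account of benefits also shifts: 4.4.1 puts reduced anemia, a clinical benefit, on the scale, while section 7 says the benefits are not clinical.

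The practical problem is where the caution sits. Section 7 adds a condition on the sign of the estimate before de-implementation is supported. Every place that acts on the result uses the bare non-inferiority label instead: the rule in 5.2, the benefit gate in 4.2 and the final sentence of section 7. A positive estimate with an upper bound below 3 points would then be both a result that does not support de-implementation and one that does. Readers of the results could cite either statement.

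**Working it through.** **Inputs.** Margin 3 points, one-sided alpha 0.025, power 89%, baseline mortality 18%, ICC 0.009, 37 clusters, 13 periods, 47 admissions per cluster-period (4.4.2); 10 sequences (3.1); expected difference zero and 22,428 episodes (4.4.1).

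**The plan's own figures first.**
- Deaths at the margin: 0.03 × 22,428 = 673, matching the stated 670 or so. Half of that: 0.015 × 22,428 = 336.
- Power: a stepped-wedge variance with a cluster random intercept and categorical periods, and power = Φ(0.03/SE − 1.96), gives 92.6–92.8% with binomial variance at 18% and 89.5–89.7% with variance at 21% (control risk plus margin). The stated 89% is therefore reproduced to within about a point under the second choice. Figure 1 is not shown, so the first step was tried at periods 2, 3 and 4, with no change in power. Without period effects power exceeds 99%, so the stated figure fits a model with them.

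**Standard error implied by 89% power.** SE = 3/(1.960 + 1.227) = 0.94 points.

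**What the 3-point rule accepts.**
- Largest estimate that meets the rule: 3 − 1.96 × 0.9415 = 1.15 points, or about 259 deaths over 22,428 episodes.
- Upper bound when the estimate is exactly 0: 1.96 × 0.9415 = 1.85 points, which is above 1.5.
- Chance, under a true null, of meeting the rule with an estimate above zero: 0.89 − 0.50 = 0.39.

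**Sensitivity to the SE.** With SE 0.88 (18% variance, 37 clusters), these become 3 − 1.96 × 0.881 = 1.27 points, 1.73 points and 0.926 − 0.50 = 0.43. With SE 0.97, the largest of the variants with period effects that were tried, they become 1.09 points, 1.91 points and 0.869 − 0.50 = 0.37.

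**The texts side by side, for an estimate between 0 and +1.15 points.**

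| Place | What it implies |
|---|---|
| 5.2 | Bound below 3: this criterion for non-inferiority is met |
| 4.2 | Once non-inferiority is concluded, testing and CO2e results may count as benefit |
| 7, margin paragraph | Does not support de-implementation |
| 7, closing paragraph | Once non-inferiority is concluded, supports de-implementation |

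**The case against.** The strongest reply is that the plan separates the statistical rule from the practice threshold on purpose and says so twice, with a cross-reference from 4.4.1 to the Discussion. It promises the estimate and the full interval, so any reader can see whether 1.5 points lies inside. It states plainly that the trial excludes harm of 3 points. The wording on both sides is hedged, and material is not the same word as unacceptable. All of this stands, and it keeps the matter to one of wording and conclusions.

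It does not remove the conflict. The cross-reference does not rescue the acceptability claim, because the paragraph it points to says smaller differences could be unacceptable. The point-estimate condition is a stated view in the Discussion, is absent from 5.2 and 4.2, and is contradicted at the end of the same section. The promise to report a half-margin difference as material, read as a point estimate, cannot apply to a non-inferior result at the planned precision, since such a result needs an estimate below about 1.15 points.

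Stronger readings are tempting and are not supported:

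- A reader might compute that with a true excess of 1.5 points the intention-to-treat bound is still met in Φ(1.5/0.94 − 1.96) = 36% of trials (34–40% over the SE variants), or that under a true null 53% are non-inferior with a bound still above 1.5, and take these for error rates. They are ordinary operating characteristics of a 3-point test. If section 7's point-estimate condition is honoured, the chance of an estimate at or below zero with a true excess of 1.5 points is only about 6%.
- A reader might infer that 1.5 points should become a second threshold for the bound. The plan sets no such threshold. It rejects margins of 1–2 points as infeasible, and power at 1.5 points would be about 36%.
- A reader might resolve the conflict by deleting the cautions in section 7. That would remove the plan's own safeguard.

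**Conclusion.** The inconsistency is real and should be corrected before outcome data are examined. Sections 4.4.1 and 7 give incompatible accounts of what 3 points means. Section 7 also contradicts itself on whether a non-inferior result with a positive estimate supports de-implementation. At the planned precision this is a common case: about 39% of trials under a true null (37–43% over the SE range).

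The figures rest on a normal approximation, the SE implied by the stated power, the intention-to-treat bound alone, and reading an excess point estimate as any estimate above zero. The per-protocol and fidelity conditions would lower the chance of declaring non-inferiority by an amount the article does not allow one to compute. Nothing here shows that the margin test, the power or the sample size is wrong. The defect lies in how the margin is justified and in what a non-inferiority label may be said to support.

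**What to change.** Keep the 3-point test, the power calculation, the sample size and the cautions in section 7. Then:

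1. In 4.4.1, replace the claim that 3 points is the largest clinically acceptable difference with the feasibility grounds already given there, and make the description of benefits agree with section 7.
2. In 5.2, 4.2 and the closing paragraph of section 7, state that non-inferiority means an excess of 3 points or more has been excluded.
3. In the same three places, make any de-implementation or benefit claim also subject to section 7's point-estimate condition.
4. Commit the report to saying whether the confidence interval includes the 1.5-point excess that the plan calls material, as a descriptive statement and not a second margin.

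The cost is wording in four places and, in some results, a less favourable headline. If the steering committee regards this as a change to the analysis plan, it follows the amendment route in section 6.2.
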